## Abstract

**Background:**

Visual stress is a reading disorder characterised by perceptual distortions, asthenopia and headache whilst reading, alongside increased sensitivity to repeated striped patterns (‘pattern glare’), in the absence of underlying ocular pathology. Coloured filters including tinted spectacle lenses and coloured overlays/acetates have been reported to ameliorate visual stress symptoms. However, evidence on coloured spectacle lenses efficacy at managing symptoms of visual stress, particularly in adults, is lacking, with recent systematic reviews advocating the need for large-scale randomised control trials.

**Methods:**

This is a double-masked randomised placebo-controlled superiority trial. University students identified with symptoms of visual stress, through use of a reading symptom questionnaire and mid-spatial frequency pattern glare test, will be recruited. Sample size for power of 90% at 5% significance, accounting for 10% dropout will be 65. Participants will be randomly assigned experimental and control coloured spectacle lenses to wear for six weeks followed by a two week washout period, prior to wear of the alternate lenses for a further six weeks with a two week washout period. Participants will compare both sets of spectacle lenses in a ‘head-to-head’ comparison after the secondary washout period, prior to choosing the preferred lenses for voluntary future wear. Long-term adherence to the preferred lenses will be assessed three months post-comparison. Researchers and participants will be masked to spectacle lenses worn throughout the duration of the trial. Reading performance will be assessed with both sets of lenses at various time points within the trial. A range of reading tests, reading symptoms and pattern glare evaluation will be used to monitor change in reading performance and visual stress symptoms during the trial.

**Discussion:**

The study will evaluate the hypothesis that coloured spectacle lenses increase reading speed and reduce severity and frequency of reading symptoms in adults with visual stress.

**Trial registration:**

The trial is registered at ClinicalTrials.gov: NCT04318106.

## Introduction

Visual Stress, occasionally referred to as ‘Meares-Irlen Syndrome’ and ‘Scotopic Sensitivity Syndrome’ is a visuoperceptual reading disorder with a reported prevalence varying between 13–96% [1] in both adults and children. Variable prevalence can be explained by the array of symptoms and signs employed to diagnose the condition, sample population tested [2,3] and unclear evidence on the underlying aetiology. Attempts have been made to standardise diagnostic criteria [3–6] however these have not been validated. Symptoms of visual stress can be broadly described as the presence of perceptual distortions, such as words and letters ‘moving’ or ‘merging’, and appearance of ‘rivers’ or coloured patterns within lines of crowded text; typically black text printed on white backgrounds [3,6]. There are several aetiologies proposed to cause visual stress but, in brief, these either fall under (i) A deficit in magnocellular processing and inability to process high temporal frequency ‘flicker’ [7,8] or (ii) Hyperexcitation of the visual cortex from repetitive black-on-white striped patterns often found in written text [9,10]. Colorimetry – the practice of determining preferred chromaticity of coloured spectacle lenses to assist with reading symptoms, is performed in some primary eyecare settings. Coloured filters, in the form of tinted spectacle lenses or sheets of coloured acetate have been reported to improve reading performance and reduce symptoms in individuals with visual stress [5,11–13] in previous randomised controlled trials and case-controlled studies.

With regard to theory (i), coloured filters are thought to supress potentially aberrant intraretinal image patterns from saccadic eye movements [7,14] and improve accuracy of ocular movements whilst reading [15] in symptomatic individuals with underlying magnocellular pathway deficits. For theory (ii) coloured filters are proposed to reduce the extent of cortical hyperexcitation by attenuating the amount of potentially aversive visual information that is received by a hyperexcitable primary visual cortex [16,17].

A few studies have investigated whether coloured lenses reduce hyperexcitability in the visual cortex associated with visual stress and/or migraines using functional neuroimaging and visual evoked potentials [16,18,19]. While some studies support a reduction in the cortical excitability with coloured filters [16] others report conflicting results [19] or only reductions in those with co-existing migraines or headaches [18]. Further work is required to fully understand the aetiology and treatment mechanisms of visual stress and what areas of the visual cortex are specifically hyperexcitable in those with visual stress.

Yet, to date investigations into the efficacy of coloured lenses at ameliorating symptoms of visual stress are scant. Recent systematic reviews conclude that a large-scale double-masked randomised control trial needs to take place to investigate coloured lens efficacy in subjects with visual stress [1,20–22]. Two meta-analyses further highlight the necessity for high quality evidence to strengthen the knowledge base in relation to coloured lens efficacy for those with reading difficulties [23,24]. Furthermore, there is some discrepancy in terms of the clinical versus statistical significance of findings of coloured spectacle lenses efficacy among previous studies. This is demonstrated by the use of percentage reading speed change noted with optimal coloured filter to determine efficacy of coloured lenses, with percentage reading speed change with optimal filters reported as ranging between 0.90% (p = 1.0) [13] and 6.4% (p = 0.03) [12].

Additionally, professional optometric bodies’ management guidance in relation to the practice of colorimetry is guarded, citing a lack of robust evidence to either endorse or reject the practice [25–27]. This protocol will detail the methods employed in a double-masked cross over randomised placebo-controlled trial. This superiority trial aims to test the hypothesis that providing coloured lenses to those with symptoms of visual stress will be effective at improving reading performance and reduce frequency of symptoms experienced whilst reading.

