## Methods and materials

### Study design

This study is designed as a double-masked cross-over randomised placebo-controlled trial of coloured lens efficacy in adults with symptoms of visual stress. The trial design is supported by the Standard Protocol Items: Recommendations for Intervention Trials (SPIRIT) framework (see supporting information S1 File). Participants will be evenly and randomly assigned one of two sets of coloured spectacle lenses for initial spectacle wear for a period of six weeks, followed by wear of an alternate pair of spectacle lenses for a further six weeks. Coloured spectacle lenses will differ in their chromaticity, with the ‘experimental’ coloured lenses, tinted to optimal chromaticity, which are presumed to reduce perceptual distortion symptoms, whilst ‘control’ lenses will comprise a chromaticity similar in perceptual colour appearance to ‘experimental’ lenses, to assist with masking, but differing in chromaticity, such that visual stress symptoms are neither improved nor worsened with use of tint. The ‘Control’ lenses shall therefore act as a placebo. Researchers and participants will both be masked to the spectacle lenses worn. A two week washout between periods of spectacle lens wear will be employed, so that any potential legacy effects of coloured lenses are negated.

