The ‘control’ lens will act as the placebo and will be sub-optimal, when compared to ‘experimental’ tint. To determine control tint, researchers will prescribe a colour that will not be aversive, yet not beneficial to the patient’s symptoms of visual stress that lies just outside the ‘Limit of Therapeutic Effect’. At the upper and lower boundary of the Limit of Therapeutic Effect, participants will consider if reading symptoms/ visual discomfort experienced are ‘worse’ or ‘no different’ compared no colour presented. The hue will be adjusted to when participants confirm that there is ‘no difference’ when compared to no colour (i.e., not beneficial nor aversive). At these two hues, the researchers propose that these are the candidate control tints. The control tint chosen will be that closest to the optimal tint on the colour diagram, to assist with participant masking – i.e., the apparent colour difference will be more visually alike between control and optimal tint. ‘Control’ tint will be of the same saturation and luminance to the ‘experimental’ tint. Researchers are mindful of previous work, stating inter-practitioner and inter-instrumental measurement error may account for ~0.03 units of chromaticity difference (the Euclidean distance between colour coordinates mapped on the 1976 CIELUV Chromaticity Diagram) between lenses [54,55]. Whilst a consistent chromatic separation between lenses will not be applied, to account for assumed difference in size of ‘Limit of Therapeutic Effect’ by observers, size of chromatic separation between lenses will be considered in post-hoc analysis of reading performance. The authors appreciate that there is a certain degree of variability in determining sub-optimal tint by this method, as demonstrated in work by Suttle and colleagues (2017) [56], whereby number of just noticeable differences between precision tints varied between 23.8 and 3.1, among 21 observers. However, researchers will aim to ensure that the ‘control’ tint be inert, through confirmation of participants’ visuoperceptual symptoms when viewing the striped body of text within the Intuitive Colorimeter™ illuminated by the assumed ‘control’ chromaticity. Furthermore, the chromaticity difference, between colour coordinates of ‘experimental’ and ‘control’ lenses will be measured by the Mark 2 SpectroCAL Spectroradiometer (Cambridge Research Systems Ltd., Cambridge, UK). Chromaticity coordinates will be plotted by computer software (Light Values Measuring System, Version 6.2.0, Windows 11.0 OS, Jeti Technische Instrumente GmbH [name], Jena, Germany). Chromaticity difference between ‘experimental’ and ‘control’ tints will be considered in post-hoc analysis of reading performance with the use of coloured lenses.

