Researchers appreciate that the studied population will be somewhat homogenous in nature (young pre-presbyopic adult undergraduate students). This trial will explore coloured lens efficacy in a cohort of subjects with a relatively equitable baseline level of reading competence, as all undergraduate students enrolled will have to exhibit demonstrable English language competence to enrol at Ulster University. Whilst this will be beneficial at controlling for amount of reading demand each participant is expected to have, irrespective of whether a benefit of coloured spectacle lenses can be rejected or endorsed, the results of this trial may need be replicated in both paediatric and general adult populations, in future investigations. Additional factors such as gender and degree studied will not be controlled for as it there is no evidence to suggest that these factors are significant in relation to visual stress. As invitation to take part will be based on subjective-reported symptom severity, one may assume a certain degree of selection bias will exist. Researchers aim to reduce selection bias through randomisation and masking of participants. Additionally, whilst risk of ascertainment bias cannot be wholly negated, the exclusion criteria for this trial is relatively uncomplicated; ensuring that only those with binocular vision anomaly/amblyopia will be excluded. Furthermore, upon trial completion, researchers will report the number of participants identified with visual stress, number who attended baseline screening, failed exclusion criteria, dropped out and were lost-to-follow-up.

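### The hypothesis is worded for coloured lenses in general, but the only randomised, masked contrast is the individually optimal hue against a nearby control hue at equal saturation and luminance

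*Protocol article*

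**What the plan says.** The hypothesis is stated twice in general terms. The Introduction will "test the hypothesis that providing coloured lenses to those with symptoms of visual stress will be effective at improving reading performance". The Discussion paragraph of the Abstract has it that "coloured spectacle lenses increase reading speed and reduce severity and frequency of reading symptoms in adults with visual stress". The main Discussion, in a sentence about replication in other populations, uses the words "irrespective of whether a benefit of coloured spectacle lenses can be rejected or endorsed".

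The design is narrower. Under Study design, participants are "evenly and randomly assigned one of two sets of coloured spectacle lenses for initial spectacle wear for a period of six weeks" and then wear the other set. The control lenses "will comprise a chromaticity similar in perceptual colour appearance to ‘experimental’ lenses, to assist with masking", and are meant to leave symptoms neither better nor worse, so that they serve as placebo. Under Interventions employed (determination of control lens), the control "tint will be of the same saturation and luminance to the" experimental tint. Of two candidate hues, "The control tint chosen will be that closest to the optimal tint on the colour diagram, to assist with participant masking". Each candidate is found by adjusting the hue until the participant reports no difference from no colour. The same section concedes some variability in locating the sub-optimal tint this way.

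Under Statistical analyses, reading speed with each lens is analysed at baseline, at spectacle collection and after six weeks. Clinically significant improvement is judged on the experimental lens against baseline, in two categories: >5% to 15%, and >15%.

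**The concern.** A superiority claim can be no wider than the contrast that randomisation and masking protect. Here that contrast lies between two tinted lenses, so whatever they share drops out of it. Expectation should drop out, since that is what a placebo is for. Any real benefit of wearing a tint of that saturation and luminance would drop out as well.

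The broad wording puts two things at stake. A positive result would support an individually chosen hue over a nearby one, but could be reported as support for coloured lenses as a class. A null result might leave a benefit common to both lenses untested. The pull will then be towards the change from baseline, which is the only comparison with no tint and is not randomised. The article expects its results to inform optometric practice, so the claim should match what the design can show.

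**Working it through.** **1. What each comparison estimates.** Let E be the true effect on reading speed of the experimental lens against no lens, and C that of the control lens against no lens. Let P be the change from baseline that would occur anyway through practice, expectation and time.

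- Experimental minus control (randomised, masked): (E + P) − (C + P) = E − C. Randomised order balances P on average.
- Experimental minus baseline (unrandomised): E + P.
- Control minus baseline (unrandomised): C + P.

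The quantity in the stated hypothesis is closest to E. The randomised contrast equals E only if C = 0.

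**2. How firmly the article supports C = 0.**

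| Requirement | What the article provides |
|---|---|
| Control inert for reading speed, the primary outcome | A rating of symptoms and comfort on text inside the colorimeter |
| Control inert over six weeks of wear | A judgement made when the tint is determined |
| Control clearly outside the therapeutic range | A hue just outside the limit, the candidate nearest the optimum, with no consistent separation applied and measurement error of about 0.03 chromaticity units cited |
| A reliable method of finding it | Variability conceded in the same section |

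Inertness is therefore intended and checked once by self-report. It is not shown on the outcome being tested.

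**3. The range.** The article gives no value for C. Assume it lies between nil and the full experimental effect. At C = 0 the randomised contrast is E; at C = E/2 it is E/2; at C = E it is 0. Nothing in the article places the trial within this range, although its own premise is the first case.

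**4. The broad wording fails even if C = 0.** If the control is inert, one of the two coloured lenses does nothing by design. A win for the experimental lens would then show that this hue works and a neighbouring hue of equal saturation and luminance does not. That is a claim about the chosen chromaticity, not about coloured lenses in general.

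**5. The baseline comparison.** The >5% to 15% and >15% categories are set for the experimental lens against baseline, so they measure E + P. No such classification is stated for the control lens, which would show how often C + P alone passes the same thresholds.

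**6. The article's sample size.** The point does not depend on it, but it bears on the cost of the fix. For a within-factors repeated measures ANOVA with m measurements, λ = N·m·f²/(1 − ρ), with df (m − 1) and (N − 1)(m − 1). The inputs are ρ = 0.5, ε = 1, α = 0.05 and power 0.90. The stated partial eta squared gives f = √(0.0355/0.9645) = 0.1919; the article prints f = 0.1985. The number of measurements is not stated.

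- m = 3, f = 0.1919: λ = 59 × 3 × 0.0368/0.5 = 13.0; power 0.901 and N = 59, the stated figure. Then 59 × 1.10 = 64.9, or 65.
- m = 3, f = 0.1985: N = 56.
- m = 2 (experimental versus control only) at N = 59: power 0.83 with f = 0.1919 and 0.85 with f = 0.1985; 90% power needs 74 or 69.

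The 59 thus fits three measurements, the same number as the analysis timepoints, better than a two-lens contrast. That is an inference from the arithmetic, not something the article states.

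**The case against.** The strongest reply is that coloured lenses is shorthand. The sentence introducing the design calls the trial placebo-controlled, and the Introduction defines colorimetry as finding a preferred chromaticity. Study design separates optimal from control chromaticity, and the close of the Discussion speaks of colorimetry and precision tinted lenses. All of that is correct. It shows that the authors know the narrower claim, which makes the correction easy. It does not alter the two statements of the hypothesis, which carry no such qualifier.

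The second reply is that the control is a placebo, set for each participant at no difference from no colour. If that holds, the randomised contrast does approximate experimental tint versus no tint. This also stands, and it limits the point. A reader might infer that a null would necessarily be misread as rejecting coloured lenses. The article does not support that: a null misleads only if the control is partly active, and the words about rejecting or endorsing a benefit are a subordinate clause, not a rule for interpreting the result.

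Third, a reader might infer that the trial examines nothing but hue. That is true of the randomised contrast only. Reading is also measured without lenses, and baseline is an analysis timepoint. Those comparisons exist but are uncontrolled.

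**Conclusion.** The point holds as a mismatch between the claim and the contrast. The hypothesis is worded for coloured spectacle lenses in general; the randomised, masked evidence will concern the individually optimal hue against a nearby hue at the same saturation and luminance. Reading it as tint versus no tint requires an inert control, an assumption the article makes and checks only by self-report in the colorimeter. Change from baseline cannot fill the gap, because it is unrandomised.

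No numerical size can be given. A reader might be tempted to combine the 0.90% to 6.4% reading-speed changes cited in the Introduction with an assumed shared fraction and derive a loss of power. The article gives no shared fraction and does not link those percentages to its planned effect size, so such figures would be arbitrary. The design itself is not shown to be wrong; the wording and the role of the baseline comparison need correcting.

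**What to change.** 1. In the Abstract and Introduction, restate the hypothesis as superiority of lenses of individually optimal chromaticity over lenses of control chromaticity at matched saturation and luminance. Bring the Discussion into line with its own closing reference to precision tinted lenses.
2. State that a null result would not exclude an effect common to both tints if the control is not inert.
3. Under Statistical analyses, label improvement with the experimental lens against baseline, including the >5% to 15% and >15% categories, as uncontrolled and not as evidence of efficacy. Report the same categories for the control lens beside it.

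The cost is a narrower claim and one extra tabulation from data already planned. The lenses, visits and randomisation do not change. The rewording does not settle whether 59 evaluable participants suffice for the two-lens contrast; that is a separate sample-size question, on which the figures under the check above bear.

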## Methods and materials

### Study design

This study is designed as a double-masked cross-over randomised placebo-controlled trial of coloured lens efficacy in adults with symptoms of visual stress. The trial design is supported by the Standard Protocol Items: Recommendations for Intervention Trials (SPIRIT) framework (see supporting information S1 File). Participants will be evenly and randomly assigned one of two sets of coloured spectacle lenses for initial spectacle wear for a period of six weeks, followed by wear of an alternate pair of spectacle lenses for a further six weeks. Coloured spectacle lenses will differ in their chromaticity, with the ‘experimental’ coloured lenses, tinted to optimal chromaticity, which are presumed to reduce perceptual distortion symptoms, whilst ‘control’ lenses will comprise a chromaticity similar in perceptual colour appearance to ‘experimental’ lenses, to assist with masking, but differing in chromaticity, such that visual stress symptoms are neither improved nor worsened with use of tint. The ‘Control’ lenses shall therefore act as a placebo. Researchers and participants will both be masked to the spectacle lenses worn. A two week washout between periods of spectacle lens wear will be employed, so that any potential legacy effects of coloured lenses are negated.

### Study population

#### Sample size calculation.

The Wilkins Rate of Reading Test reading speed has been used as the outcome measure for an improvement with use of coloured filters [12,13,28–31]. Sample size was calculated using statistical software (G-Power, Version 3.19.4, 2024), for an a priori within-factors repeated measures ANOVA of the Wilkins Rate of Reading Test (the primary outcome measure of this trial). A partial eta squared (${\eta \rho }^{2}$) of 0.0355 was used with a conservative small to medium effect size (f) of 0.1985. Probability of a type-1 error (α), of 0.05 and power (1−β) of 0.90 were applied. Correlation among repeat measures was assumed 0.5 and nonsphericity correction (ϵ) was held at 1.0. A sample size of 59 participants was determined appropriate for this investigation The required sample size has been increased by 10% to account for attrition. Therefore, 65 participants shall be recruited for the trial.

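### The stated 90% power is not established for experimental versus control lenses: 59 is reproduced only as a three-measurement omnibus test, and a two-lens comparison on the same inputs needs 69 to 74 completers

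*Protocol article*

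**What the plan says.** The abstract calls the trial a placebo-controlled superiority trial and states: "Sample size for power of 90% at 5% significance, accounting for 10% dropout will be 65". The Introduction describes the design: "This protocol will detail the methods employed in a double-masked cross over randomised placebo-controlled trial". Under Study design, the control lens is the placebo.

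The section Sample size calculation says the number was obtained in G*Power "for an a priori within-factors repeated measures ANOVA of the Wilkins Rate of Reading Test (the primary outcome measure of this trial"). Its inputs are:

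- effect size: a partial eta squared "of 0.0355 was used with a conservative small to medium effect size (f) of 0.1985";
- correlation: "Correlation among repeat measures was assumed 0.5";
- nonsphericity correction: "was held at 1.0";
- type 1 error 0.05 and power 0.90.

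The result is "A sample size of 59 participants was determined appropriate for this investigation". Then: "The required sample size has been increased by 10% to account for attrition", which gives 65.

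The section does not give the number of measurements entered, and does not say whether the powered effect is time, lens or their interaction. Statistical analyses plans a repeated measures ANOVA of reading speed for both interventions at three timepoints: baseline, spectacle collection and six weeks. No section gives a power or sample size for experimental versus control.

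**The concern.** A placebo-controlled superiority crossover asks one main question: do people read faster with the experimental lens than with the control lens? That is a two-level, within-person contrast, and a reader of the abstract will attach the 90% to it.

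An omnibus within-subject test over three measurements answers a different question. It can be significant because reading speed changes with practice, or because any tinted lens differs from none, with no difference between the two lenses. Power for the omnibus test does not carry over to the lens contrast.

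A null result is where this matters. The Discussion criticises earlier trials as underpowered and expects this one to inform practice. If the lens comparison is not significant, it will be read against a 10% chance of missing the planned effect. That figure has not been shown to apply.

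**Working it through.** **Inputs** (Sample size calculation): α = 0.05; power 0.90; ρ = 0.5; ε = 1.0; partial η² = 0.0355; printed f = 0.1985; N = 59.

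**Step 1. Are the two effect sizes the same?** f = √(η²/(1 − η²)) = √(0.0355/0.9645) = 0.1919. Conversely, f = 0.1985 implies η² = 0.0394/1.0394 = 0.0379. They differ, so both are carried forward.

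**Step 2. Reproduce 59.** G*Power's within-factors test uses a noncentral F with λ = N·m·f²/(1 − ρ), df1 = m − 1 and df2 = (N − 1)(m − 1), where m is the number of measurements. Smallest N for 90% power:

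| m | f = 0.1919 | f = 0.1985 |
|---|---|---|
| 2 | 74 | 69 |
| 3 | **59** | 56 |
| 4 | 50 | 47 |
| 5 | 44 | 41 |
| 6 | 39 | 36 |
| 7 | 35 | 33 |
| 8 | 33 | 31 |

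Only m = 3 with f = 0.1919 returns 59. There λ = 59 × 3 × 0.03681/0.5 = 13.03 on 2 and 116 df, and power is 90.1%. With f = 0.1985 and m = 3, power at 59 is 92.0%. The alternative parameterisation that drops the correlation term (λ = (N − 1)(m − 1)f²) does not give 59 for any m from 2 to 8; its closest value is 69.

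**Step 3. Two lenses, same f and ρ.** With m = 2 and N = 59, λ = 59 × 2 × f²/0.5 on 1 and 58 df.

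- f = 0.1919: λ = 8.69, power 82.6%; 90% needs 74 completers.
- f = 0.1985: λ = 9.30, power 85.1%; 90% needs 69 completers.

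A paired t test with d_z = 2f/√(2(1 − ρ)) = 2f (0.384 or 0.397) gives the same powers. If all 65 recruits completed, power would be 86.1% or 88.3%.

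**Step 4. If f describes three means instead.** The lens contrast is then one pair out of three, and its size depends on the pattern. With ρ = 0.5 the standardised paired difference equals the difference between the two means in SD units. At N = 59, two-sided 0.05:

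| Pattern of the three means | Difference between the pair | Power, f = 0.1919 to 0.1985 |
|---|---|---|
| Evenly spaced, extreme pair | f√6 = 0.470 to 0.486 | 94% to 96% |
| One differs from two equal ones | 3f/√2 = 0.407 to 0.421 | 87% to 89% |
| Evenly spaced, adjacent pair | f√1.5 = 0.235 to 0.243 | 43% to 45% |

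If the two lenses are the equal pair in the second pattern, there is no lens difference at all, yet the omnibus test keeps its 90% (f = 0.1919) to 92% (f = 0.1985).

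**Step 5. Sensitivity to the correlation.** For two lenses at f = 0.1919 and N = 59, ρ = 0.60 gives 90.0% and ρ = 0.70 gives 96.3%.

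**The case against.** The strongest reply is that 83% to 85% is no firmer than the 90%. If three measurements were entered, f is the spread of three means, and moving it unchanged to two lenses sets the lens difference at 2f, about 0.38 to 0.40 SD, which the protocol never states. This stands. The 83% to 85% is one conditional case, and a reader who took it as the trial's actual power would go further than the document allows.

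Second, three measurements are inferred. A reader might conclude that the calculation powers change across baseline, collection and week six. The three timepoints in Statistical analyses make that plausible, but no lens, experimental and control is also a possible set of three, since the test is read with and without lenses. The document does not settle it. This limits what can be said about which hypothesis was powered. It does not rescue the 90%, because either set gives an omnibus test and two levels cannot yield 59 with either effect size at correlation 0.5.

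Third, the sizing matches the planned ANOVA, and the abstract ties its 90% to no contrast. The match is real, but an omnibus within-subject test is still not the placebo comparison.

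Fourth, the correlation may exceed 0.5, since each visit averages two readings from the same person. That may be so, but the protocol assumes 0.5 and justifies nothing higher.

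Fifth, the harm is limited. The estimates and the type 1 error are unaffected, and effect sizes with confidence intervals are promised. This bears on severity.

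**Conclusion.** The concern holds in a limited form. The 90% power in the abstract and the sample-size section is not established for experimental versus control lenses. The figure of 59 is reproduced only as a three-measurement, 2-df test with f = 0.1919, and a two-lens comparison at correlation 0.5 needs 74 or 69 completers.

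The size of the gap depends on what f means. If it is meant for two lenses, power at 59 completers is about 83% to 85%, a shortfall of 5 to 7 points. If it describes three means, power lies between about 43% and 96%, and the document does not say where.

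It does not follow that the trial is underpowered in fact, or that it needs more participants: at f = 0.1919 a correlation of about 0.60 would bring the two-lens figure to 90%. The fault lies in the stated power claim. Severity: should be fixed.

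**What to change.** In Sample size calculation and in the abstract:

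1. Name experimental minus control Wilkins Rate of Reading Test speed at six weeks as the powered contrast.
2. Replace the two conflicting effect sizes with one, expressed as a paired difference with its within-person SD or correlation.
3. Restate the power, or the detectable difference, at 59 completers for that contrast. If the present f and the correlation of 0.5 are kept for two lenses, that is about 83% (f = 0.1919) to 85% (f = 0.1985).
4. Remove the 90% claim for the lens comparison unless a higher correlation is justified.

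The cost is rewording two paragraphs and probably a less favourable stated power. Recruitment, visits and measurements do not change.
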